## Abstract

**Background:**

Nudge strategies are well-established in behavioral economics as effective approaches for promoting desirable behaviors. However, the potential benefits of integrating nudge-based strategies into pharmacist-led patient education have not yet been demonstrated. Here, we present a study protocol for an interventional trial to address this issue.

**Methods:**

The PHARM-NUDGE study is a multicenter, randomized, parallel-group, single-blind, controlled trial prospectively designed to evaluate whether nudge-based pharmacist-led education can promote patients’ preventive behaviors against skin toxicities associated with cancer chemotherapy. The key inclusion criteria are as follows: (1) patients who are men or women and aged 18 years or older and (2) patients scheduled to receive a chemotherapy regimen containing capecitabine, liposomal doxorubicin, lenvatinib, cetuximab, or panitumumab in outpatient chemotherapy units or during hospitalization. The enrolled patients are randomly assigned in a 2:1 ratio to the nudge-based education or standard education groups. Pharmacists responsible for patient education utilize special educational tools that incorporate nudge strategies and provide skincare education to patients assigned to the nudge-based education group. Patients assigned to the standard education group receive skincare education with equivalent content but without nudges. The primary endpoint is the proportion of patients in each group who achieve four or more of the five predefined behavioral criteria.

**Conclusions:**

The PHARM-NUDGE study is the first randomized controlled trial to evaluate the potential benefits of integrating nudge strategies into pharmacist-led skincare education for patients undergoing cancer chemotherapy with a high risk of skin toxicity, with patient enrollment initiated on October 15, 2025. Completion of the trial and acquisition of the final results are eagerly anticipated.

**Trial registration:**

This trial was registeredwith the Japan Registry of Clinical Trials (clinical trial number: jRCT1040250089, registration date: September 3, 2025).

**Supplementary Information:**

The online version contains supplementary material available at 10.1186/s40780-026-00556-4.

## Background

Skin toxicities, which are often symptomatic and can affect patients’ quality of life, are among the most common adverse events during cancer chemotherapy. Certain types of skin toxicities are strongly associated with specific anticancer agents, including hand–foot syndrome (HFS) induced by fluoropyrimidines and acneiform rash induced by epidermal growth factor receptor inhibitors. Severe skin toxicity may result in dose reduction and treatment discontinuation in patients with cancer [1]. Management and treatment of these skin toxicities have been established and include systemic antibiotics and topical steroids [2]. In addition to these medical interventions, patient self-care practices to minimize skin irritation play an important role in the prevention and mitigation of skin toxicities [3].

Clinical practice guidelines recommend that patients at risk for HFS use skin moisturizers without alcohol, avoid mechanical stress (including long walks or heavy carrying), and avoid chemical stress (including solvents or disinfectants) [4, 5]. In addition, a randomized phase III trial demonstrated that the prophylactic use of 10% urea cream was more effective than non-urea moisturizers in preventing HFS [6]. For patients at risk of acneiform rash induced by epidermal growth factor receptor inhibitors, avoiding frequent hot-water washing and using a sunscreen with high sun protection factor are recommended as part of routine skincare [4, 5]. Although desirable skincare behaviors have been established through previous clinical trials and clinical experience, it should be emphasized that these behaviors are ultimately carried out by patients themselves rather than by healthcare professionals. Pharmacists seek to promote preventive skincare behaviors by educating patients prior to cancer chemotherapy. However, a survey conducted in Japan reported that patient adherence to voluntary skincare behaviors was not necessarily high [7]. Even the behavior with the highest adherence—applying a moisturizer—was performed by only 74.1%, whereas the behavior with the lowest adherence—using sunscreen on exposed areas—was reported by only 14.1% [7].

In behavioral economics, a “nudge” refers to a strategy that alters the choice environment to encourage desirable behaviors without coercion or financial incentives [8]. Nudge-based strategies are increasingly being integrated into clinical settings to promote desirable behaviors among patients and healthcare professionals. A representative example is the use of default options in electronic prescribing systems, in which setting generic drugs as the default has been shown to substantially increase prescription rates for generic drugs compared with brand-name drugs, while preserving clinicians’ discretion [9]. Although the demand for nudge-based approaches in healthcare is increasing, the effect of nudge-based patient education on promoting voluntary skincare behaviors among patients undergoing cancer chemotherapy with a high risk of skin toxicity remains unclear.

The PHARM-NUDGE (PHARMacist-led patient education with NUdges to promote Dermatological self-care during chemotherapy: a General Education-controlled) trial is a multicenter, randomized, parallel-group, single-blind, controlled trial prospectively designed to evaluate the potential benefits of integrating nudge-based strategies into patient education by pharmacists.

## Methods

### Study type, registration, and ethics

The PHARM-NUDGE trial is a multicenter, randomized, parallel-group, single-blind (patient-blinded), controlled trial, with patient enrollment initiated on October 15, 2025. This study is being conducted at Hamamatsu University Hospital (Hamamatsu, Japan), Cancer Institute Hospital of the Japanese Foundation for Cancer Research (Tokyo, Japan), and Hamamatsu Medical Center (Hamamatsu, Japan). This trial was registered with the Japan Registry of Clinical Trials (clinical trial number: jRCT1040250089, registration date: September 3, 2025) and was approved by the Ethics Committee of the Hamamatsu University School of Medicine (approval number: 25–133).

### Patients

The key inclusion criteria are listed in Table 1. Eligible patients must meet all of the following criteria: (1) male or female patients aged 18 years or older; (2) patients scheduled to receive a chemotherapy regimen containing capecitabine, liposomal doxorubicin, lenvatinib, cetuximab, or panitumumab in outpatient chemotherapy units or during hospitalization; and (3) patients who provide written informed consent to participate in this trial. Patients who remain hospitalized between the first and second cycles of chemotherapy are excluded from the study because evaluating changes in voluntary behavior at home would be difficult. The other exclusion criteria are listed in Table 1.

**Table 1 Tab1:** Key inclusion and exclusion criteria

Key inclusion criteria
1. Male or female patients aged 18 years or older
2. Patients scheduled to receive a chemotherapy regimen containing capecitabine, liposomal doxorubicin, lenvatinib, cetuximab, or panitumumab in outpatient chemotherapy units or during hospitalization
3. Patients who provide written informed consent to participate in this trial
**Key exclusion criteria**
1. Patients with impaired activities of daily living
2. Patients who are unable to communicate effectively
3. Patients for whom the evaluation of this study would be difficult because of underlying disease or comorbidities
4. Patients for whom participation in this study would be difficult because of neurological or psychiatric disorders
5. Patients who remain hospitalized between the first and second cycles of chemotherapy
6. Patients presenting with significant dermatological adverse events at the time of enrollment because of prior treatment
7. Patients with an Eastern Cooperative Oncology Group performance status of two or higher
8. Patients deemed inappropriate for participation by the attending physician or principal investigator

All inclusion criteria must be met for enrollment. Patients meeting any of the exclusion criteria will be excluded

### Study design

An overview of the PHARM-NUDGE study is presented in Fig. 1. The enrolled patients are randomly assigned in a 2:1 ratio to the nudge-based education plus standard education or standard education alone groups. Randomization is performed using block sizes of three and six, which vary randomly, and is stratified according to the cancer chemotherapy regimen administered to each patient. Two study visits are scheduled for each participant: visit 1 on the first day of the chemotherapy regimen and visit 2 on the day of the second administration. At visit 1, each participant receives pharmacist-led education on preventive skincare practices depending on their assigned group (nudge-based education plus standard education or standard education alone). Patients’ self-care behaviors at home are assessed at visit 2. After enrollment, all participants are followed for eight weeks to assess skin toxicity.

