### Patient education

The pharmacists responsible for patient education in the PHARM-NUDGE study use special educational tools that incorporate nudge strategies and provide skincare education to patients assigned to the nudge-based education group at visit 1. We prepared two types of educational tools that incorporate several nudges and simplified messages, tailored to the specific features of different skin toxicities (Fig. 2). One tool is designed for patients scheduled to receive chemotherapy regimens containing capecitabine, liposomal doxorubicin, or lenvatinib, which are strongly associated with HFS or hand–foot skin reaction. The other tool is prepared for patients scheduled to receive chemotherapy regimens containing cetuximab or panitumumab, which are strongly associated with acneiform rash. Example sentences from our educational tools, along with their respective nudge types, are presented in Table 2. Patients assigned to the standard education group receive skincare education using the actual tools and explanations used in daily clinical practice at each study institution. In our study design, patients assigned to the nudge-based education group will receive additional explanatory materials on measures to prevent and manage skin toxicities, in addition to general information materials about chemotherapy. To avoid any effects on outcomes from distributing the additional materials themselves, independent of the nudge elements, we also provided patients in the standard education group with supplementary materials on skin toxicities that did not include any nudge elements (Supplementary Fig. S1). Additionally, to minimize differences in educational content and time spent between the two groups, we plan to provide pharmacists responsible for patient education with prior instruction on key points and time allocation.

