### Subgroup analyses

Stratified analyses will be performed by sex, chemotherapy regimen, cancer type, prior treatment status, enrollment institution, and the pharmacist who provides patient education.

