In the PHARM-NUDGE study, randomization is performed using the stratified permuted block method with a 2:1 allocation ratio. Stratified randomization is reasonable for small trials in which treatment outcomes may be affected by known clinical factors [11]. In our trial, the chemotherapy regimen administered to each participant was selected as a stratification factor because it is strongly associated with cancer type, sex, age, and the incidence of dermatological adverse events, all of which may create heterogeneity in the environment and influence patients’ behavioral decisions. The allocation ratio was set at 2:1 to ensure that a larger number of participants are assigned to the nudge-based education group to obtain a more precise 95% CI estimate for this group. The PHARM-NUDGE study was designed not primarily to demonstrate the superiority of nudge-based education over standard education, but to accurately estimate the effect size of nudge-based education in the target population.

In this trial, we prepared special educational tools that incorporate nudge-based approaches (Fig. 2 and Table 2). Loss aversion, a fundamental concept in behavioral economics, refers to the tendency for people to be more sensitive to potential losses than to equivalent gains [12]. A representative example of loss aversion is vaccination promotion. Wang et al. showed that loss-framed messaging significantly increases COVID-19 vaccine acceptance [13]. The watching eye effect is a psychological phenomenon whereby people are more likely to engage in prosocial behaviors when they feel that others are watching them. Gaube et al. showed that visual eye cues improved hand hygiene compliance among healthcare workers [14]. In the PHARM-NUDGE study, although visual eye cues are not used, the educational tools clearly state that patients’ self-care behaviors at home would be checked at their next visit, thereby creating a psychological sense of being observed by healthcare workers. Social norms refer to individuals’ tendency to follow behaviors that are common or expected within a group. For example, telling adolescents with epilepsy how well their peers took their medications increased adherence [15]. Loss aversion, watching eye effects, and social norms have been established as nudge-based approaches, and their effectiveness is anticipated in the PHARM-NUDGE study.

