The primary endpoint of the PHARM-NUDGE study was defined according to the behavioral criteria for assessing patients’ self-care behaviors (Table 3). Using moisturizers and avoiding skin irritation are recommended as basic self-care measures in clinical practice guidelines [4, 5]. Therefore, it is important to encourage patients to engage in these behaviors. However, evidence demonstrating that these behaviors can prevent skin toxicity remains inconclusive. A randomized phase III study evaluated the effect of a structured teaching model incorporating intensive prophylactic measures (including routine use of emollients three to four times a day and wearing loose-fitting clothes and shoes) on the prevention of capecitabine-induced HFS; however, the intervention did not demonstrate a statistically significant difference [16]. Although our trial included the incidence of dermatological adverse events as a secondary endpoint, it may be challenging to detect a statistically significant difference between the two groups.

In the PHARM-NUDGE trial, our primary objective is to estimate the incremental effect of integrating nudge-based strategies into standard patient education. To ensure standardization of baseline educational practices, responsibility for patient education was assigned to a single healthcare professional. Nevertheless, we believe that this nudge-based approach is not inherently limited to pharmacists and may be adaptable to other healthcare professionals in future implementations.

Our study protocol has potential limitations. Firstly, differences in the educational materials or in pharmacists’ explanations may allow participants to infer their assigned group. To address this issue, we plan to inform participants only that two types of educational approaches are being compared, without disclosing that a special educational tool will be provided exclusively to one group. Secondly, although we described the study design as a single-blind trial in the Methods section, it is not possible to fully blind the differences in the educational materials between the two groups. Therefore, it should be noted that the trial is not fully single-blinded.

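### Usual education differs by hospital, but the between-arm difference is fixed as a crude pooled estimate: avoidable random error from site imbalance, and a standardisation claim that needs rewording

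*Protocol article*

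**What the plan says.** Methods, Study design: "The enrolled patients are randomly assigned in a 2:1 ratio to the nudge-based education plus standard education or standard education alone groups". The scheme uses permuted blocks of 3 or 6 in random order, and allocation "is stratified according to the cancer chemotherapy regimen administered to each patient". The Discussion repeats that "the chemotherapy regimen administered to each participant was selected as a stratification factor", citing its link with cancer type, sex, age and skin toxicity. Institution is not mentioned as a factor in either place. Three hospitals take part (Study type, registration, and ethics).

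Methods, Patient education: standard education is given "using the actual tools and explanations used in daily clinical practice at each study institution". The same section adds two measures meant to keep the arms comparable: nudge-free supplementary material for controls, and advance instruction of the educating pharmacists on content and timing. Data collection and management adds that the pharmacists who interview at Visit 2 are trained.

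Discussion: "To ensure standardization of baseline educational practices, responsibility for patient education was assigned to a single healthcare professional".

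Statistical analysis: the CI for the between-arm difference comes from Formula 2, the unadjusted Wald interval. Subgroup analyses: the factors include "enrollment institution, and the pharmacist who provides patient education".

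**The concern.** The outcome is self-care behaviour after education, so a hospital's usual teaching is a direct input to it. That teaching is local, and because the nudge arm receives standard education plus the nudge tool, it forms the background in both arms. Nothing in the allocation holds the 2:1 ratio within a hospital. With about 40 controls over three hospitals, the control group can by chance lean towards a hospital whose usual education is stronger or weaker. A pooled difference then contains part of the difference between hospitals. The Discussion says the trial is meant chiefly to estimate the effect size accurately, so removable noise in that estimate deserves attention.

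The wording is a second issue. The Discussion credits standardised baseline education to the use of one profession, whereas Patient education keeps each hospital's own tools and explanations in use. The planned subgroup by educating pharmacist shows that several individuals teach, so the sentence cannot mean one person.

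**Working it through.** **1. The plan's own figures.** Inputs from Sample size calculation: 70/80 and 20/40.
- Nudge: 0.875 ± 1.96 × √(0.875 × 0.125/80) = 0.803 to 0.947.
- Standard: 0.500 ± 1.96 × √(0.5 × 0.5/40) = 0.345 to 0.655.
- Difference: 0.375, SE = √(0.875 × 0.125/80 + 0.25/40) = 0.087, CI 0.204 to 0.546.

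All agree with the printed values after rounding. The yardstick is the SE of 8.7 points.

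**2. How uneven can a hospital's share be?** Assumptions: 120 patients, 80 to nudge, allocation unrelated to site (hypergeometric). Site sizes are not in the document, so 40 and 60 are assumed. Let a hospital enrol n patients, of whom k go to nudge. The between-arm difference in its share is k/80 − (n − k)/40, with SD √[f(1 − f) × (120/119) × (1/80 + 1/40)], where f = n/120.

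| Hospital size | SD of share difference | More than 10 points | More than 15 points |
|---|---|---|---|
| 60 | 0.097 | 33% | 8% |
| 40 | 0.092 | 22% | 10% |

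The tails are strict, because exact ties occur. With n = 60, a 44:16 split gives 0.55 − 0.40 = exactly 0.15 and is not counted. With n = 40, a 24:16 split gives 0.30 − 0.40 = exactly −0.10 and is not counted.

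**3. Effect on the arm difference.** Suppose that hospital differs from the other two by a gap g in success rate; g of 0.20 to 0.30 is assumed. The shift is g × share difference.
- n = 60: SD 0.20 × 0.097 = 1.9 points to 0.30 × 0.097 = 2.9 points.
- n = 40: SD 0.20 × 0.092 = 1.8 points to 0.30 × 0.092 = 2.8 points.
- As a fraction of the variance, for n = 60: (1.9/8.7)² = 5% to (2.9/8.7)² = 11%.
- In the 8% tail for n = 60, the first split counted is 45:15, a share difference of 0.5625 − 0.375 = 0.1875. The shift there is at least 0.20 × 0.1875 = 3.75 points to 0.30 × 0.1875 = 5.6 points.

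**4. Simulation of the planned scheme.** 6,000 runs per scenario, N = 120, 2:1, permuted blocks of 3 and 6. Assumed: five regimen strata, three equal hospitals, and nudge rates centred on 0.875. Results are in points, under regimen-only randomisation.

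| Control rates at the three hospitals | SD of shift | 95th percentile of absolute shift | SD of estimate, crude | SD of estimate, Mantel-Haenszel |
|---|---|---|---|---|
| 0.40, 0.50, 0.60 | 1.3 | 2.6 | 8.8 | 8.7 |
| 0.30, 0.50, 0.70 | 2.6 | 5.0 | 8.8 | 8.5 |
| 0.20, 0.50, 0.80 | 3.6 | 7.1 | 8.7 | 8.1 |

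The mean shift is zero throughout, and crude Wald coverage is about 94% with or without differences between hospitals. With unequal shares (45/45/10%) and no hospital differences, the SDs are 8.66 crude and 8.72 adjusted. Adjusting therefore costs almost nothing when it is not needed.

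**The case against.** A reader might infer that the pooled difference is biased by hospital. The document does not support that. Randomisation makes the imbalance zero on average, and the Wald interval already reflects the extra variation. What is left is a modest loss of precision.

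A reader might also infer that standardisation fails altogether. That too goes further than the text. The nudge-free supplement, the common instruction of educators and the trained interviewers may all narrow hospital differences, and local teaching is common background and not only a feature of the control arm. The two education measures, however, are aimed at differences between the arms, and each hospital's own tools stay in use. The wording conflict therefore stands, in a narrower form.

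Three further points are fair. Institution is not ignored, since a stratified analysis by institution is planned. It is listed as a subgroup analysis, though, and about 40 controls split over three hospitals give noisy separate results, not an adjusted overall estimate. The choice of regimen as the stratification factor is reasoned. Finally, the between-arm difference is formally a secondary endpoint, the primary being the per-arm proportions. The Discussion nevertheless names the incremental effect as the primary objective, so the estimator for the difference matters.

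A separate analysis plan could add a site-adjusted estimate. The article, however, names the crude Formula 2 for this contrast, so the point concerns a stated choice and not an omission.

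**Conclusion.** The point holds as a modest and cheap improvement in precision, together with a wording correction. Under the assumed site sizes and a 20 to 30 point hospital gap, chance imbalance contributes an SD of about 2 to 3 points, against an SE of 8.7 points. Adjustment reduces the SD of the estimate by 0.1 to 0.6 points in the simulated scenarios, and by nothing if hospitals do not differ. Site shares and hospital success rates are not in the document, so these are ranges under assumption and not estimates for this trial. The hypergeometric figures also ignore the regimen strata; where regimen use differs by hospital, regimen stratification would give some balance on site.

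It might seem to follow that the randomisation should be changed. Enrolment began on October 15, 2025, the gain is small, and regrouping strata would loosen the balance on regimen that the sponsor chose deliberately. That step is not justified here.

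**What to change.** 1. In Statistical analysis, prespecify an institution-stratified risk difference with 95% CI for the between-arm contrast, reported with Formula 2. Mantel-Haenszel weights over the three hospitals would serve: Σwᵢ(p₁ᵢ − p₂ᵢ)/Σwᵢ, with wᵢ = n₁ᵢn₂ᵢ/(n₁ᵢ + n₂ᵢ). Name the variance estimator, and fix this before outcomes are compared by arm. The per-arm proportions and their CIs stay as planned.
2. In the Discussion, replace the claim that using one profession ensures standardisation. Say that education is delivered by pharmacists, using site-specific usual education with common prior instruction.

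Cost: institution is already recorded for the subgroup analysis, so this needs one extra estimate and one reworded sentence. The only statistical downside is a trivial loss of precision if hospitals do not differ. Allocation and enrolment are unaffected.
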